## Abstract

**Background:**

Anaemia is a common health problem among pregnant women and a contributing factor with a major influence on maternal mortality in Indonesia. The Four Pillars Approach is a new approach to anaemia in pregnancy, combining four strategies to improve antenatal and delivery care. The primary objective of this study is to measure the effectiveness of the Four Pillars Approach. The barriers, the facilitators, and the patients’ as well as the midwives’ satisfaction with the Four Pillars Approach will also be measured.

**Methods/Design:**

This study will use a cluster randomised controlled trial. This intervention study will be conducted in the Public Health Centres with basic emergency obstetric care in Yogyakarta Special Province and in Central Java Province. We will involve all the Public Health Centres (24) with emergency obstetric care in Yogyakarta Special Province. Another 24 Public Health Centres with emergency obstetric care in Central Java Province which have similarities in their demographic, population characteristics, and facilities will also be involved. Each Public Health Centre will be asked to choose two or three nurse-midwives to participate in this study. For the intervention group, the Public Health Centres in Yogyakarta Special Province, training on the Four Pillars Approach will be held prior to the model’s implementation. Consecutively, we will recruit 360 pregnant women with anaemia to take part in part in the study to measure the effectiveness of the intervention. The outcome measurements are the differences in haemoglobin levels between the intervention and control groups in the third trimester of pregnancy, the frequency of antenatal care attendance, and the presence of a nurse-midwife during labour. Qualitative data will be used to investigate the barriers and facilitating factors, as to nurse-midwives’ satisfaction with the implementation of the Four Pillars Approach.

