### Setting

The Yogyakarta Special Province has a total of 24 Public Health Centres with emergency obstetric care which we will use in our study. Based on the population criterias (such as the prevalence of anaemia in pregnancy, cultural background, health insurance), demographic characteristics (such as accessibility and location of the Public Health Centre), and facilities (such as laboratory, medical devices, and emergency kit) available in the Public Health Centre with emergency obstetric care, we will choose another 24 Centres (the same number as are in Yogyakarta) for our control group. Central Java Province has many similarities with Yogyakarta Special Province. The Provincial Health Offices of Central Java Province gave us the information about the Public Health Centres with obstetric emergency care in some districts of Central Java Province which surround Yogyakarta Province, and which we could use as research fields. Based on this information, we will randomly choose the 24 Public Health Centres for our control group. In total, we will involve 48 Public Health Centres as our research fields. Generally, there are about seven to ten nurse-midwives in every Public Health Centre eligible, according to the inclusion criteria. Considering the other health services that should be handled by the nurse-midwives in Public Health Centre and the activities that should be conducted by the nurse-midwives if they are involved in the study, the head of Public Health Centres permitted to involved only two or three nurse-midwives in this study. These are the nurse-midwives who will be trained and who will treat all pregnant women with anaemia according to the study protocol. The nurse-midwives who have been selected, still have the right not to participate in our study. We estimate 90% of nurse-midwives will join our study.

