### Participants

#### Nurse-midwives

The inclusion criterias for the nurse-midwives in the intervention and control groups are: they hold a three year diploma in nursing-midwifery education, and they work on a daily basis in Public Health Centres with basic emergency obstetric care. All participants will be required to sign a consent form.

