### Intervention

#### Training of the Four Pillars Approach

This training will be given to the nurse-midwives in order to introduce the new concept of the Four Pillars Approach in managing pregnant women with anaemia, and training them how to implement this model in Public Health Centres with emergency obstetric care. Based on international literature and experts’ opinion, we will develop a training module for the Four Pillars Approach in managing pregnant women with anaemia. At the end of this training, the nurse-midwives will have the knowledge and skill to manage pregnant women with anaemia based on the Four Pillars Approach.

The training will last eight hours, and consist of two sessions. The first session will be held in-class, and the second session will take place in the skills laboratory of the Nursing School of the Universitas Gadjah Mada Yogyakarta. A specialist in obstetrics and gynaecology, a senior teacher and a senior nurse will take part as teachers during the in-class session. Different educational methods will be used, such as power point slides, video and role play. In the skills laboratory session, training participants will be divided into six groups; each group consisting of ten to eleven participants. Every group will be directed by one tutor and one “simulated patient” (a person who acts like a pregnant women with anaemia). Case scenario, drama, demonstration and role play will be used to capture a real-life situation. All participants will be assessed and are required to pass this. The tutor will observe the competency of each nurse-midwife, and give an assessment to each participant based on the observation check list. There are four items to be observed by the tutor: procedure of treatment, communication, professional behaviour, and data registration. Those items are scored by using a Likert scale 1 – 3. Score 1 will be given if the performance of the nurse-midwife is unsatisfactory, score 2 if the performance is reasonable but could still be improved upon, and score 3 if the performance of the nurse-midwife is excellent and complete according to the protocol. All the nurse-midwives are required to pass this assessment exam with a minimum score of 60%.

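### Each centre chooses its two or three study nurse-midwives knowing its arm, so provider selection could differ by arm and be counted as an intervention effect

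*Protocol article*

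**What the plan says.** **Arm is fixed by province.** The Abstract states: "For the intervention group, the Public Health Centres in Yogyakarta Special Province, training on the Four Pillars Approach will be held prior". All 24 such centres in Yogyakarta are used. For Central Java, the Setting section states: "we will randomly choose the 24 Public Health Centres for our control group". The random step there samples control centres; it does not allocate centres to arms.

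**The centre makes the choice, from a larger pool.** The Abstract states: "Each Public Health Centre will be asked to choose two or three nurse-midwives to participate in this study". The Setting section adds: "Generally, there are about seven to ten nurse-midwives in every Public Health Centre eligible, according to the inclusion criteria". The eligibility criteria, the same in both arms, are that "they hold a three year diploma in nursing-midwifery education, and they work on a daily basis in Public Health Centres" with basic emergency obstetric care. No rule is given for choosing among those who qualify. The reason given for the limit of two or three is workload, and those selected may decline: "We estimate 90% of nurse-midwives will join our study".

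**The chosen providers carry the trial.** Of them the Setting section says: "These are the nurse-midwives who will be trained and who will treat all pregnant women with anaemia according to the study protocol". Under Study population, nurse-midwives also recruit the women. Under Outcome measures, their records supply the count of antenatal visits, which is a primary outcome.

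**The analysis.** Data analysis and model building names the intervention indicator and patient characteristics as model terms, with baseline haemoglobin for the haemoglobin outcome. It names no provider characteristic.

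**The concern.** The selection rule is worded identically for both arms, but the task is not the same. An intervention centre decides whom to send for eight hours of training with an assessment, and who will then lead the two parenting classes. A control centre decides only who gives usual care within the study. Because the arm is known, the reasons for naming someone, and that person's reasons for declining, can differ between arms.

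The traits a centre might plausibly select on are knowledge, skill and professional behaviour. The Background section makes these the third and fourth pillars, that is, part of the mechanism under test. If intervention centres sent stronger staff than control centres named, a difference that predates training could not be told apart from the effect of training.

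The selection happens inside each centre. Matching centres on population, location and facilities does not address it, and nor does adjustment for patient characteristics. A random intercept for centre accounts for clustering; it does not remove a difference that lines up with arm.

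**Working it through.** No stated figure in the article is in dispute here. The check asks how selective the choice can be and what it could be worth on the haemoglobin scale.

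**Share of eligible staff taken (Abstract, Setting).** Lowest 2/10 = 20%; highest 3/7 = 43%. There is room for selection.

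**How many are chosen per centre.** The Training section plans six groups of ten to eleven, so 60 to 66 trainees.
- Choosing two per centre: 24 × 2 = 48, and 90% of 48 = 43.2.
- Choosing three per centre: 24 × 3 = 72, and 90% of 72 = 64.8.
- Working back: 60/0.9 = 66.7 and 66/0.9 = 73.3 chosen, which over 24 centres is 2.8 to 3.1.

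The article's own training numbers therefore point to about three per centre.

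**Strength of selection under perfect ranking.** The expected mean of the top three of *n* standard normal values, by simulation, is 0.82 for *n* = 7, 0.92 for *n* = 8 and 1.06 for *n* = 10. The chosen group would average 0.82 to 1.06 SD above its centre's mean on the trait used for ranking.

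**Conversion to haemoglobin.** Shift = (selection in SD) × (correlation of that trait with the nurse-midwife's effect on haemoglobin) × (between-midwife SD of that effect).
- Correlation: 0.5, an assumption.
- Between-midwife SD: 0.1 to 0.32 g/dl, an assumption. The upper value is the between-centre SD implied by the Power calculation, 1.01 × √0.10 = 0.32. It also contains case mix and local differences, so it is not a midwife SD. The lower value corresponds to about 1% of haemoglobin variance, (0.1/1.01)² = 0.0098.
- Control arm: no selection on the trait, an assumption.

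| | SD 0.1 g/dl | SD 0.32 g/dl |
|---|---|---|
| Top 3 of 7 | 0.82 × 0.5 × 0.1 = 0.04 | 0.82 × 0.5 × 0.32 = 0.13 |
| Top 3 of 10 | 1.06 × 0.5 × 0.1 = 0.05 | 1.06 × 0.5 × 0.32 = 0.17 |

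Against the 0.5 g/dl target, 0.04/0.5 = 8% and 0.17/0.5 = 34%. If both arms choose in the same way, the selection terms cancel and the shift is zero.

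**The case against.** The strongest reply is that the rule is symmetric. Every centre in both arms chooses under the same two criteria, and the only rationale given is workload. Choice by rota availability fits the text at least as well as choice by ability. This stands: the documents leave the route open but do not show that it is taken. Differential refusal also has no known direction, because a heavier intervention workload could lose the most capable staff as easily as the least.

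The size can also be challenged. It assumes perfect ranking in every intervention centre and none in control centres, and the documents give no between-midwife SD. That stands too, so the range is a hypothetical ceiling and not an estimate. For skilled birth attendance the link may be weaker, since that outcome comes from centre or hospital records and the attendant need not be a chosen nurse-midwife.

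Three stronger readings are tempting and are not supported.
- *The exam is an extra filter in the intervention arm.* The Training section does say "All the nurse-midwives are required to pass this assessment exam with a minimum score of 60" per cent. But the assessment follows the training and so belongs to the intervention, and nothing says that a nurse-midwife who fails is dropped or replaced. On a raw total, a score of 2 on all four items gives 8/12 = 67%, a pass.
- *Yogyakarta heads choose after hearing about the model at the seminar.* Monitoring of the study places the seminar before the training, but nowhere before the choice of nurse-midwives.
- *The shift could reach 0.20 g/dl.* That needs two chosen from ten (1.27 × 0.5 × 0.32 = 0.20), which fits poorly with 60 to 66 trainees from 24 centres.

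Finally, centres know their arm because allocation is by province, which is a larger and separate flaw. That is true, but balancing the provinces would not remove selection within centres.

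**Conclusion.** The point holds as an open route to bias created by a stated method: discretionary choice of providers, made with the arm known, and no provider term named in the model. It is not evidence that the arms will differ. The possible haemoglobin shift runs from zero, if both arms choose alike, to a hypothetical ceiling of about 0.04 to 0.17 g/dl (8% to 34% of the 0.5 g/dl target). That ceiling rests on about three chosen per centre, perfect ranking in the intervention arm only, a correlation of 0.5 and a between-midwife SD of 0.1 to 0.32 g/dl. Only the number per centre can be inferred from the article; the rest are assumptions. The change is worth making because it is cheap and replaces the stated method with a less biased one.

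**What to change.** Reword the Abstract (Methods/Design) and the Setting section so that, in both arms:

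- the centre supplies a list of all its eligible nurse-midwives;
- the research team draws two or three at random from that list;
- a nurse-midwife who declines is replaced by the next in the drawn order;
- refusals are recorded and reported by arm.

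This keeps the number the heads of centres have permitted and needs no extra study staff or patients. The cost is protocol wording, one list per centre and a draw. The downside is that heads lose some rota freedom, which may need to be agreed with them given the workload reason for the limit, and that some of those drawn may be less keen. The change makes provider selection comparable between arms; it does not cure the confounding that comes from allocating by province, which has to be dealt with separately.

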**Discussion:**

If the Four Pillars Approach is effective in improving the outcome for pregnant women with anaemia, this approach could be implemented nationwide and be taken into consideration to improve the outcome for other conditions in pregnancy, after further research.

**Trial registration:**

Current Controlled Trials ISRCTN35822126.

## Background

Anaemia is a significant health problem among pregnant women in Indonesia with a major impact on maternal mortality [1]. The World Health Organization (WHO) defines anaemia as a condition where the level of haemoglobin (Hb) in the blood is less than 11 g/dl [2]. Nutrional anaemia in pregnancy is found to be the most prevalent in Indonesia [3]. Other factors causing anaemia such as HIV, malaria and hookworm infection are also found in several areas in Indonesia [4,5]. One of the endemic areas for malaria is Kulonprogo, one of the districts in Yogyakarta Special Province [5].

The 2007 Indonesia Demographic and Health Survey reported the prevalence of anaemia in pregnancy of 28% [6]. A similar prevalence was found in Yogyakarta in 2009 [7]. Concerning maternal health indicators in Indonesia, only 59.8% of births are attended by skilled birth attendants [8] and less than 70% of pregnant women attend no more than four antenatal care visits [9]. The antenatal care use is also influenced by the knowledge of patients and other family members [10].

Studies on maternal health services and the quality of nursing-midwifery care in Indonesia, found that nurse-midwives have a lack of knowledge and skills to identify the risk factors in pregnant women, and that their professional behaviour is sub-standard [11-13]. Also the antenatal care attendance of pregnant women is low, resulting in a poor quality of antenatal care [14]. The studies suggested that antenatal care training for nurse-midwives be improved, as an important strategy to help solve these problems [11-14]. One of the studies showed that women have negative perceptions about the quality of maternity care, caused by the nurse-midwives’ impolite, negligent behaviour and intentional humiliation of the women (such as verbal abuse) [13].

Studies from other low-income countries suggested the importance of counselling and health education for pregnant women with anaemia to improve their knowledge and awareness about a healthy pregnancy [15-19]. One study advised that booklets should be given to increase women’s knowledge about Iron Deficiency Anaemia (IDA) and mother and child health [16]. All studies expressed an urgent need for training programs for nurse-midwives to improve the quality of health services, including the detection of anaemia risk during pregnancy [16,17].

The WHO stressed the importance of antenatal care visits to maintain the health status of the mother and the wellness of the foetus [20]. A study which evaluated the effectiveness of an early antenatal health promotion workshop found that a healthy lifestyle during pregnancy correlated with maternal and infant health outcomes [21]. The support of the husband or other family members, and a caring attitude from the nurse-midwife proved to motivate pregnant women to attend the available antenatal care services [22-24].

Based on the result of these studies, experts’ opinion and indepth interviews with nurse-midwives, we designed a Four Pillars Approach to synergize the empowerment between pregnant women and nurse-midwives. These four pillars are: a healthy lifestyle during pregnancy, social support from the husband or other family members, adequate knowledge and skills of the nurse-midwives, and the nurse-midwives’ professional behaviour.

The first and second pillars (healthy lifestyle and the strengthening of social support) represent patient empowerment. The nurse-midwives empowerment is represented by the third and fourth pillars: adequate knowledge and skills, and the professional behaviour of nurse-midwives.

In this study, we will evaluate the effect of the Four Pillars Approach on pregnant women with anaemia.

### Objectives

#### Primary objective

To measure the effectiveness of the Four Pillars Approach in the management of pregnant women with anaemia.

#### Secondary objective

To investigate the barriers and facilitating factors of the implementation of the Four Pillars Approach, as well as nurse-midwives’ satisfaction with the approach.

## Methods/Design

### Study design

This study will use a cluster randomised controlled trial design [25], measuring outcomes on individual level of the included pregnant women with anaemia. Individual outcomes between intervention and control group will be compared.

The nurse-midwives involved in the intervention group will be trained in the Four Pillars Approach prior to the implementation of this model. The nurse-midwives will follow a refresher course on current management of anaemia in pregnancy, therapeutic communicaton (counselling) and professional behaviour. They will also have practical guidance in the skill laboratory phase where they have to demonstrate their knowledge and skills to manage pregnant women with anaemia such as taking laboratory tests, carry out physical examination on the signs and symptoms of anaemia, and communcation in terms of giving health education to patients.

Then, the trained nurse-midwives in all Public Health Centres with emergency obstetric care in the intervention group will provide antenatal care services based on the Four Pillars Approach to the pregnant women with anaemia. Meanwhile, in the control group all Public Health Centres with emergency obstetric care will provide their usual antenatal care services to the pregnant women with anaemia.

In an intervention study, the effectiveness of antenatal care given by trained nurse-midwives to pregnant women with anaemia, following the Four Pillars Approach, will be compared to the usual care given. The usual care is the routine antenatal care carried out by nurse-midwives with a three year diploma in nursing-midwifery education.

### Setting

The Yogyakarta Special Province has a total of 24 Public Health Centres with emergency obstetric care which we will use in our study. Based on the population criterias (such as the prevalence of anaemia in pregnancy, cultural background, health insurance), demographic characteristics (such as accessibility and location of the Public Health Centre), and facilities (such as laboratory, medical devices, and emergency kit) available in the Public Health Centre with emergency obstetric care, we will choose another 24 Centres (the same number as are in Yogyakarta) for our control group. Central Java Province has many similarities with Yogyakarta Special Province. The Provincial Health Offices of Central Java Province gave us the information about the Public Health Centres with obstetric emergency care in some districts of Central Java Province which surround Yogyakarta Province, and which we could use as research fields. Based on this information, we will randomly choose the 24 Public Health Centres for our control group. In total, we will involve 48 Public Health Centres as our research fields. Generally, there are about seven to ten nurse-midwives in every Public Health Centre eligible, according to the inclusion criteria. Considering the other health services that should be handled by the nurse-midwives in Public Health Centre and the activities that should be conducted by the nurse-midwives if they are involved in the study, the head of Public Health Centres permitted to involved only two or three nurse-midwives in this study. These are the nurse-midwives who will be trained and who will treat all pregnant women with anaemia according to the study protocol. The nurse-midwives who have been selected, still have the right not to participate in our study. We estimate 90% of nurse-midwives will join our study.

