## Discussion

The high prevalence of anaemia in pregnancy in Yogyakarta Special Province requires adequate nursing-midwifery care to prevent the adverse effects of anaemia in the perinatal period. Learning from the experiences of other low income countries in handling similar conditions, and considering the nurse-midwives’ views, we developed an innovative approach, called the Four Pillars Approach to antenatal care.

Our primary objective is to evaluate the effectiveness of the Four Pillars Approach in managing pregnant women with anaemia, indicated by a difference in haemoglobin level in pregnancy, improving the frequency of antenatal care attendance and skilled birth attendance during labour. In addition, the secondary objective of this study is to explore the barriers and the facilitating factors of the implementation of the Four Pillars Approach and to evaluate the patient’s and nurse-midwives’ satisfaction with the Four Pillars Approach.

The Four Pillars Approach will be implemented by the trained nurse-midwives in the Public Health Centres in Yogyakarta Special Province. It is expected that this approach will be effective in managing anaemia in pregnancy in order to prevent perinatal morbidity and mortality. If the Four Pillars Approach is effective in improving the outcome of pregnant women with anaemia, this approach could be implemented nationwide and be taken into consideration to improve the outcome for other conditions in pregnancy, after further research.

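### The study is called cluster randomised, but arm is fixed by province: the only random step samples control centres, so arm and province are the same variable

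*Protocol article*

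**What the plan says.** Under Study design the protocol article states: "This study will use a cluster randomised controlled trial design". The Methods/Design paragraph of the abstract uses the same label.

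The allocation it then describes is by province:

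- Abstract, Methods/Design: "We will involve all the Public Health Centres (24) with emergency obstetric care in Yogyakarta Special Province", and these are named as the intervention arm: "For the intervention group, the Public Health Centres in Yogyakarta Special Province, training on the Four Pillars Approach will be held" before implementation starts.
- Discussion: "The Four Pillars Approach will be implemented by the trained nurse-midwives in the Public Health Centres in Yogyakarta Special Province".
- Setting: candidate control centres lie "in some districts of Central Java Province which surround Yogyakarta Province, and which we could use as research fields". From these, "Based on this information, we will randomly choose the 24 Public Health Centres for our control group".

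Setting also lists similarity criteria for control centres (anaemia prevalence, culture, insurance, access, location, facilities). It does not say how selection on these criteria combines with the random draw.

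Under Primary outcome, the Hb change from T0 to T1 is compared between groups. Under Data analysis and model building, a non-zero intracluster correlation (ICC) leads to a random-intercept model for women clustered in centres. The model contains the intervention indicator and patient characteristics, and T0 Hb is added when T1 Hb is modelled.

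**The concern.** Randomisation to arm requires that a centre could have fallen into either arm by chance. Here every Yogyakarta centre is certain to be in the intervention arm and every Central Java centre is certain not to be. Drawing 24 centres at random from a Central Java list makes the controls more representative of that list. It does nothing to balance the arms.

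The stated design property is what lets a reader attribute a difference to the intervention. Without it, a province difference in antenatal use, in birth attendance or in the course of Hb through pregnancy is estimated together with the Four Pillars effect, and the planned p-value carries no allowance for it. The abstract and Discussion say that nationwide use could follow if the approach proves effective, so the strength of the evidence matters.

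**Working it through.** **Allocation, read side by side.** Let A = 1 for an intervention centre and P = 1 for a Yogyakarta centre. From the abstract, Setting and Discussion, A = P for all 48 centres (24 with A = P = 1, 24 with A = P = 0). A model containing both terms cannot be estimated. The centre intercept describes how centres scatter around their arm mean; a shift shared by all 24 centres of one province moves that mean and goes into the arm coefficient. More women or more centres would not change this.

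**The plan's own sample size.** Inputs from Power calculation: two-sided α 0.05 (two-sided is assumed), power 0.80, ICC 0.10, dropout 20%, 180 women per arm. Women per centre: 360/48 = 7.5 recruited, 7.5 × 0.8 = 6 analysed. Design effect = 1 + (6 − 1) × 0.10 = 1.5.

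| Outcome | Independent n per arm | Total = 2 × n × 1.5 / 0.8, each arm rounded up |
|---|---|---|
| Hb, 0.5 g/dl, SD 1.01 | 65 | 244 |
| Birth attendance, 50% vs 70% | 93 | 350 |
| Visits, 1, SD 2.1 | 70 | 264 |

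Birth attendance drives the size, and 350 is within 3% of the stated 360. The sample size is not in dispute.

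**Planned precision.** Analysed per arm: 180 × 0.8 = 144. Effective per arm: 144/1.5 = 96.

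- Hb: SE = 1.01 × √(2/96) = 0.146 g/dl
- Birth attendance, 50% in both arms: SE = √(2 × 0.25/96) = 0.072
- Visits: SE = 2.1 × √(2/96) = 0.303

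**Sensitivity to a residual province difference.** With no intervention effect and a residual difference b, the rejection rate is P(|Z + b/SE| > 1.96). The values of b are assumptions.

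| Outcome | b | b/SE | Rejects |
|---|---|---|---|
| Hb | 0.1 g/dl | 0.69 | 10.5% |
| Hb | 0.2 g/dl | 1.37 | 28% |
| Hb | 0.3 g/dl | 2.06 | 54% |
| Birth attendance | 10 points | 1.39 | 28% |
| Visits | 0.25 | 0.82 | 13% |
| Visits | 0.5 | 1.65 | 38% |

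For Hb, b is what remains after T0 is taken into account, not the raw difference between provinces. All the values of b shown are smaller than the effects the trial is powered to detect (0.5 g/dl, 20 points, one visit).

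**Same point as a variance.** If province carries a fraction f of total variance, then in units of that variance the true variance of the difference is 2/96 + 2f, while the analysis uses 2/96. With f = 0.01 the ratio of standard errors is √(0.0208/0.0408) = 0.714, and 1.96 × 0.714 = 1.40 gives a type I error of about 16%. With f = 0.005 it is about 11%, and with f = 0.02 about 25%.

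**The case against.** The strongest defence is that the plan works to make the provinces comparable. Controls are chosen on relevant criteria, including laboratory facilities, and come from neighbouring districts. Women with HIV, malaria or hookworm are excluded in both arms. Hb is compared as change from T0, and the model enters T0 Hb and patient characteristics. This stands as mitigation. It can shrink a province difference but cannot separate it from the intervention.

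It also limits what may be claimed about Hb. A reader might infer that any provincial difference in Hb level or laboratory practice would be reported as a Four Pillars effect. The article does not support that. An offset present at both T0 and T1 largely cancels in a change score, and entering T0 Hb removes much of it. Only a province difference in T1 Hb given T0, or in the change, biases the Hb result. Antenatal visits and skilled birth attendance have no comparable protection, because no baseline for them is described.

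A reader might also take the rejection rates as the bias in this trial. They are not: the article reports no province difference, so the rates show only how sensitive the test would be.

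The defence that a journal article condenses its full protocol does not help. The point does not rest on a missing randomisation method. It rests on a positive statement of allocation by province.

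Finally, separating the arms geographically has a practical rationale, although the article does not give one: it limits contamination. That is a reason to keep the allocation, not to call it randomised.

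**Conclusion.** The label is wrong as written. Allocation is by province, the random step is sampling of control centres, and arm is completely aliased with province. This follows from the text alone and needs no assumption.

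The size of the consequence is conditional. With 96 effective women per arm and no intervention effect, residual province differences of 0.2 g/dl, 10 points and half a visit would turn a nominal 5% test into one that rejects in about 28%, 28% and 38% of trials. These figures assume 6 analysed women per centre, ICC 0.10, the planning SDs and a normal test. They ignore any gain in precision from covariates, which would lower the SE and so raise the rejection rate for the same residual difference. The exposure is greater for visits and birth attendance than for Hb.

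It does not follow that the trial will give a false result, that the sample size is wrong, or that within-province randomisation is the only acceptable remedy.

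**What to change.** **Required.** In the abstract, in Study design and wherever else the label is used, replace *cluster randomised* with *non-randomised cluster-controlled trial, allocation by province*. Describe the draw of Central Java centres as sampling, and say how it combines with the similarity criteria. In the analysis section, state that p-values and confidence intervals exclude between-province variation. Limit the planned conclusion to an adjusted association between provinces rather than randomised evidence of effectiveness. The cost is wording and a weaker claim; women, centres and the model stay the same.

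**Option, if allocation is still open.** Randomise 12 of the 24 centres within each province and fit province as a fixed effect. This keeps 48 centres, 24 trained centres and 360 women, and makes the province term estimable. The costs are real:

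- Training travel for 12 Central Java centres.
- The Yogyakarta seminar under Monitoring of the study would have to be restricted, or control centres there would be briefed on the model.
- Contamination would dilute the effect. Birth attendance has little reserve: with 96 effective women per arm, power is 0.81 for 20 points. If contamination cut that to 18 points (assumed), power is Φ[(0.18√96 − 1.96√(2 × 0.59 × 0.41)) / √(0.25 + 0.68 × 0.32)] = Φ(0.585), about 0.72.

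This is therefore a trade-off for the investigators, whereas the relabelling is needed for as long as allocation stays by province.
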